#### Study plan

This study will be conducted in two phases (Fig. 1):Screening (2 weeks): Trained researchers in the hospital will explain this trial to and seek written informed consent from potentially eligible patients. Patients who agree to participate in the study will undergo BMD measurements, laboratory investigations, and an ECG. The results of these tests will be conveyed by telephone and patients who meet the inclusion criteria will be randomized within 2 weeks after the screening visit.Treatment (12 weeks): On the second visit, patients will be randomly assigned to one of the two groups (the BHH10 group or the placebo group) and supplied with their allocated investigational drugs after completing the DSKI and EQ-5D questionnaires. Participants will take two tablets of BHH10 or placebo three times daily for 12 weeks. Additional visits will be made at monthly intervals during the 12 weeks of treatment. A total of four visits will be made during the treatment period. A blood test will be conducted 8 weeks after randomization (visit 4). BMD measurements, blood and urine tests, and an ECG will be performed 12 weeks after randomization (visit 5).

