#### Primary outcome measurement

The primary outcome will be the change in BMD at the lumbar spine (L1–4) between baseline (visit 1) and 12 weeks after randomization (visit 5). BMD will be examined by dual-energy X-ray absorptiometry. Both participating institutions use the same type of X-ray machine (Lunar Prodigy, GE Medical Systems Lunar, Madison, WI, USA).

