### Sample size

The primary null hypothesis of this study is that there is no difference in the change in BMD at the lumbar spine (L1–4) between the BHH10 and placebo groups after 12 weeks of treatment. In view of the results of a similar study of herbal medicine in postmenopausal women with osteoporosis [16], a mean difference of 0.047 ± 0.097 between the experimental group and control group was assumed. With a 5% significance level and a power of 80%, it was calculated that a sample size of 66 patients per group would be necessary. Allowing for a dropout rate of 20%, a sample size of 168 participants (84 in each group) has been included.

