### Statistical analysis

The analysis data set will consist of an intention-to-treat data set, a per protocol (PP) data set, and a safety data set. The intention-to-treat data set will include all subjects assigned to each group. The PP data set will include only participants who adhered to the study protocol and completed the clinical study. The minimum compliance rate for participants taking the investigational drugs in the PP data set is 80%. The safety data set will include any participants who were randomly assigned to and received at least one dose of the investigational drug. The intention-to-treat analysis will be the primary analysis and will be compared with the PP analysis in a sensitivity analysis. The last observation carried forward method will be used to manage missing data.

For the descriptive analysis, the two-sample Student’s *t*-test or Wilcoxon rank sum test will be used for continuous data and the chi-squared test or Fisher’s exact test will be used for categorical data depending on whether the data are normally distributed or skewed.

For the confirmatory analysis, the primary efficacy endpoint, the change in BMD at the lumbar spine (L1–4) between baseline and 12 weeks, will be evaluated using Student’s *t*-test or the Wilcoxon rank sum test. The secondary endpoints will be evaluated using Student’s *t*-test or the Wilcoxon rank sum test for continuous data or the chi-squared test or Fisher’s exact test for categorical data. We will perform a regression analysis to examine the causal relationship between the DSKI, EQ-5D, and the primary outcome. All statistical analyses will be performed by a statistician blinded to treatment allocation using SAS (version 9.4, SAS Institute Inc., Cary, NC, USA). A significance level of 5% will be used.

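### With one post-baseline BMD scan, LOCF assigns zero change to every woman without that scan, so any true effect is diluted in the primary estimate

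*Protocol article*

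**What the plan says.** All references are to the protocol article.

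- **Missing data** (Statistical analysis): "The last observation carried forward method will be used to manage missing data". The ITT analysis is primary, and "The intention-to-treat data set will include all subjects assigned to each group". The only sensitivity analysis named is the comparison with the per-protocol set.
- **Primary outcome** (Primary outcome measurement): this is defined as "change in BMD at the lumbar spine (L1–4) between baseline (visit 1) and 12 weeks after randomization (visit 5").
- **Schedule** (Study plan): at screening, "Patients who agree to participate in the study will undergo BMD measurements, laboratory investigations, and an ECG". At the end, "BMD measurements, blood and urine tests, and an ECG will be performed 12 weeks after randomization (visit 5"). In between, the text mentions only this: "A blood test will be conducted 8 weeks after randomization (visit 4"). The schedule figure is not available here, but no passage describes another scan.
- **Sample size**: "Allowing for a dropout rate of 20%, a sample size of 168 participants (84 in each group) has been included".
- **Withdrawn women** (Data management): those who consent to it still have the scheduled tests at their last visit.
- **Secondary endpoints**: femoral BMD, the bone turnover markers, DSKI and EQ-5D are each defined by one baseline value (visit 1 or 2) and one visit-5 value.

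**The concern.** LOCF needs an intermediate measurement to carry forward. The text describes none for BMD, so the rule becomes baseline carried forward: a woman without a later scan enters the primary test with a change of exactly 0, as if it had been measured. If the mean change is not zero, that value is systematically wrong for her.

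Three things are at stake.

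- The size of any effect is understated, in a trial whose Abstract says it could provide the foundation for phase III.
- The reported interval is centred on the diluted value and looks tighter than an interval from complete data.
- If the two arms lose different shares of women, the zeros enter unequally. The withdrawal criteria include adverse events and unsatisfactory effect, both of which may depend on arm.

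The sample size section treats the 20% as lost, whereas the analysis keeps them as zeros. The per-protocol comparison does not test this assumption, because it removes non-completers.

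**Working it through.** **Inputs from the Sample size section:** difference 0.047, SD 0.097, 5% significance (two-sided assumed), 80% power, 66 per group, 20% dropout, 84 per group. **Assumptions not in the documents:** missing at random, mean placebo change 0 unless stated, unscanned women share the arm's true mean change, and the dropout splits by arm.

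**1. The plan's own figure.** n = 2 × [0.097 × (1.960 + 0.842) / 0.047]² = 66.86 per group, which agrees with the stated 66 apart from rounding. 67 / 0.8 = 83.75, so 84 per group and 168 in total. The stated size reproduces.

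**2. Formulas under zero-change imputation.** With unscanned share d and true mean change μ in an arm:
- expected arm mean = (1 − d)μ
- arm variance = (1 − d) × SD² + d(1 − d)μ²
- SE of the difference = √[(v₁ + v₀)/84]

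**3. All 20% unscanned, equally in both arms.**
- Expected difference = 0.8 × 0.047 = 0.0376, a shortfall of 0.0094 (20%).
- v₁ = 0.8 × 0.097² + 0.16 × 0.047² = 0.00788; v₀ = 0.8 × 0.097² = 0.00753.
- SE = √[(0.00788 + 0.00753)/84] = 0.0135.
- SE with complete data: 0.097 × √(2/84) = 0.0150. SE with observed cases (0.8 × 84 = 67.2 per arm): 0.097 × √(2/67.2) = 0.0167.
- Bias / SE = 0.0094/0.01354 = 0.69. Coverage of 0.047 = Φ(1.96 + 0.69) − Φ(−1.96 + 0.69) ≈ 0.89. Simulation of 40,000 trials gave 0.892.
- Power: 79.3% with LOCF, 80.2% with observed cases.

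**4. Other unscanned shares, equal in both arms.**

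| Unscanned | Expected difference | SE, LOCF | SE, observed cases |
|---|---|---|---|
| 5% | 0.0446 | 0.0146 | 0.0154 |
| 10% (half of the 20% scanned) | 0.0423 | 0.0143 | 0.0158 |
| 20% | 0.0376 | 0.0135 | 0.0167 |
| 30% | 0.0329 | 0.0127 | 0.0179 |

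At 10%, bias / SE = 0.0047/0.0143 = 0.33 and coverage is about 93.8%.

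**5. No drug effect, equal dropout.** Expected difference 0; simulated type I error 5.1%.

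**6. No drug effect, unequal dropout.** With 10% vs 30% unscanned and a common change of −0.02, the spurious difference is 0.9 × (−0.02) − 0.7 × (−0.02) = −0.004. With the arms reversed it is +0.004. SE is 0.0134 and type I error about 6.0% (simulated 5.9%).

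**7. True effect 0.047, placebo change 0, unequal dropout.** LOCF power is 88.1% (BHH10 10%, placebo 30%) or 67.8% (BHH10 30%, placebo 10%), against 79.6% for observed cases.

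**The case against.** **A reader might infer that every dropout is set to zero.** The documents do not support that. Under Data management, withdrawn women who agree still have the final tests, and some withdrawal criteria, such as low compliance judged at the final evaluation, do not imply a missing scan. Treating all 20% as unscanned is the worst case within the planned allowance.

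**A reader might infer that the standard error is wrong.** It is not wrong for what is being estimated. The simulated spread of the zero-imputed estimator is 0.0135, equal to its SE. The loss of coverage comes from the bias alone; without it, coverage would be 95%. What remains is that the result looks more precise (0.0135) than complete data would (0.0150).

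**A reader might infer that the estimate is always biased or the test invalid.** With equal random dropout and no drug effect there is no bias, and the type I error is 5%. The 20% shortfall also assumes that unscanned women would have had the full 12-week effect. If they stopped early and gained less, the shortfall against a treatment-policy target would be smaller.

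**The type I error figure rests on assumptions.** Neither a 10% vs 30% split nor a common change of 0.02 is in the documents. With 5% vs 15% and the same change, the figure is about 5.2%. One might cite regression to the mean as the source of a common change, since the screening scan also selects women. But the inclusion criterion names no skeletal site, so selection on the lumbar value cannot be presumed.

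None of this removes the central point: a woman without a post-baseline scan is given zero change in the primary analysis by a rule that the article states outright.

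**Conclusion.** The concern holds for women without a post-baseline BMD. If BHH10 has an effect, the primary estimate is diluted by the unscanned share. Under the planning values, a placebo change of 0 and unscanned women sharing the full effect, the shortfall is 10% if half of the planned 20% are scanned and 20% if none are, with coverage of about 93.8% and 89% respectively. The test itself is nearly unaffected when dropout is equal and random. If dropout differs by arm and the mean change is not zero, the bias can take either sign; the one null example worked here moves the type I error from 5% to about 6%, on assumed inputs. This is a stated rule that yields a wrong estimate, not a detail left to an analysis plan. It rests on the schedule as described in the text; an intermediate BMD scan shown only in the schedule figure would change it.

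**What to change.** Before unblinding, replace LOCF as the primary missing-data method with one that does not impute zero change. Choose a single primary analysis: ANCOVA of visit-5 lumbar BMD on arm and baseline BMD, under missing at random, using every observed visit-5 value, including those of withdrawn women who were scanned. Multiple imputation with the same covariates would give nearly the same answer, because there is no intermediate BMD to add information, so both are not needed.

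Add a placebo-based or delta-adjusted sensitivity analysis, and keep LOCF at most as a further sensitivity analysis. Report the number of unscanned women by arm. Apply the same rule to the secondary endpoints that have one baseline and one visit-5 value.

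The cost is protocol and analysis-plan wording and modest programming, with no new patients or data. The SE becomes larger: about 0.0167 with 20% missing, before any gain from baseline adjustment, which cannot be sized from the documents. Recruitment ended in April 2018 and the article appeared in September 2018, so the sponsor should confirm that the blind is still intact. If it is not, the change should be reported as made after unblinding.

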### Design and setting

This study is a phase II multicenter, randomized, placebo-controlled clinical trial with two parallel groups. Participants who voluntarily sign informed consent and are eligible for this study will be assigned randomly to one of two groups (the BHH10 or the placebo group) in a 1:1 allocation. Patients will take two tablets of BHH10 or placebo three times daily for 12 weeks.

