#### Recruitment strategy

The study participants were recruited competitively from two sites of the Acupuncture and Moxibustion Department of Kyung Hee University Hospital of Korean Medicine, either Hoegidong or Gangdong in Seoul, Korea. A total of 168 postmenopausal women with osteoporosis were recruited via broadcast media, newspapers, posters, and the Internet homepages of the participating hospitals, as well as advertisements placed in nearby welfare centers. Recruitment started in March 2016 and the accrual target was reached in April 2018.

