### Types of participant

#### Inclusion criteria

Participants must be women who meet the following criteria:Ambulatory and aged 55–85 yearsPostmenopausal (at least 12 months since the last menstrual period)BMD should be below −2.5 standard deviationsWilling to participate and sign a consent form after being given a detailed explanation of the trial

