### Randomization and allocation concealment

For randomization, an independent blinded statistician will generate random numbers using the SAS randomization program (version 9.4; SAS Institute, Inc., Cary, NC, USA). The manufacturer will supply the hospital with investigational drugs in consecutively numbered drug containers with identical packaging to conceal treatment allocation. Blinded researchers in each hospital will enroll and assign participants to one of the two study groups.

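### The confirmatory test of change in lumbar BMD is valid but unadjusted; prespecifying ANCOVA on baseline BMD would generally add precision at almost no cost

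*Protocol article*

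**What the plan says.** The Statistical analysis section sets the confirmatory comparison: "the primary efficacy endpoint, the change in BMD at the lumbar spine (L1–4) between baseline and 12 weeks, will be evaluated using Student’s *t*-test" or, as the alternative, the Wilcoxon rank sum test. The continuous secondary endpoints get the same pair of tests. No covariate is named anywhere in the article. The one regression planned relates DSKI and EQ-5D to the primary outcome and is not described as an adjusted comparison of the arms.

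Baseline lumbar BMD is part of the endpoint definition, so it will be on file: "The primary outcome will be the change in BMD at the lumbar spine (L1–4) between baseline (visit 1) and 12 weeks after randomization (visit 5"). Visit 1 is the screening visit, and one inclusion criterion is that BMD "should be below −2.5 standard" deviations; the skeletal site for that cut-off is not named.

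Allocation is 1:1. On the random list the article says that "an independent blinded statistician will generate random numbers using the SAS randomization program", with no stratification or balancing factor mentioned. Participants were "recruited competitively from two sites", and the Primary outcome measurement section says that both sites use the same type of densitometer.

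**The concern.** Subtracting baseline removes its influence completely only if week-12 BMD rises one-for-one with baseline. Measurement error and biological variation usually make the slope smaller than 1. Change is then correlated with baseline, and that correlation remains as noise in an unadjusted comparison of change. If the arms differ on baseline by chance, part of the difference also carries into the estimated effect, with its sign reversed.

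ANCOVA estimates the slope from the data and targets the same mean difference. At stake are the width of the confidence interval, some power, and how far the result of this one trial depends on the luck of the baseline draw. Type I error is not at stake.

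**Working it through.** **Inputs.** From the Sample size section: difference 0.047, SD 0.097 (no unit given, and not stated whether this is the SD of change or of a single visit), 5% significance, 80% power, 66 per group, 20% dropout, 168 in total. Rho is not in the document, so a range is shown.

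**The plan's own figure.** For a two-sided, unadjusted comparison of two means:

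n per group = 2 × [0.097 × (1.960 + 0.842) / 0.047]² = 66.9, rounded up to 67 against the stated 66. Then 67 / 0.8 = 83.75, so 84 per group and 168 in total. The trial was therefore sized for an unadjusted two-sample test.

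**Variance of the two analyses.** With equal SD s at both visits:

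- Var(change) = 2s²(1 − rho)
- Var(ANCOVA) = s²(1 − rho²)
- ratio = (1 + rho)/2, so the saving is (1 − rho)/2

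**Power and sample size if 0.097 is the SD of change.** Power = Φ(0.047 / [0.097 × √((1+rho)/2) × √(2/67)] − 1.96). The required n per group is 66.9 × (1+rho)/2, rounded up.

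| Analysis | Variance saving | Power, 67 per arm | n per group for 80% power |
|---|---|---|---|
| Unadjusted change | – | 80% | 67 |
| ANCOVA, rho 0.5 | 25% | 90% | 51 |
| ANCOVA, rho 0.7 | 15% | 86% | 57 |
| ANCOVA, rho 0.9 | 5% | 82% | 64 |
| ANCOVA, rho 0.95 | 2.5% | 81% | 66 |

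At rho 0.98 the saving is 1%.

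**Which rho fits the plan's SD?** If 0.097 is the SD of change, rho = 1 − 0.097²/(2s²). An assumed single-visit SD of 0.10 gives rho 0.53 and a saving of 24%; 0.16 gives rho 0.82 and 9%. A rho of 0.95 would need s = 0.097/√0.10 = 0.31.

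**If 0.097 is a single-visit SD.** At rho 0.7 the SD of change is 0.097 × √0.6 = 0.075, and the unadjusted test already has about 95% power with 67 per arm. At rho 0.9 it has more than 99.9%. The gain in power is then slight or nil.

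**If selection narrows the baseline spread.** The formula assumes equal variances. As an illustration with assumed values, take slope 0.9, residual variance 0.19 and baseline variance cut from 1 to 0.3:

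- Follow-up variance = 0.81 × 0.3 + 0.19 = 0.433
- Observed rho = 0.27/√(0.3 × 0.433) = 0.75, for which the formula predicts a saving of 12.5%
- Var(change) = 0.1² × 0.3 + 0.19 = 0.193 and Var(ANCOVA) = 0.190, a true saving of only 1.6%

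**Chance imbalance.** Assume a baseline SD of 0.1 and rho 0.5. A one-standard-error baseline difference moves the unadjusted estimate by (1 − 0.5) × 0.1 × √(2/n):

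- 84 per arm: 0.0077, about 16% of 0.047
- 67 per arm: 0.0086, about 18% of 0.047

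**The case against.** The strongest case against is that nothing here is an error. A two-sample test of change is valid under randomization, controls type I error and is unbiased over repeated randomizations, and the sample size was calculated for it. With a highly reproducible measure such as BMD, rho could be near 1 and the gain only 1–3% of variance. The larger figures rest on a rho that the article does not give and on one reading of 0.097. Supportive adjusted analyses may also exist in an analysis plan that is not shown.

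Most of this stands, and it rules out three stronger readings:

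- A reader might infer that the plan ignores baseline BMD. It does not: the change score subtracts it, and only about (1−rho) of an imbalance remains.
- A reader might infer that selecting women on a low scan biases the comparison through regression to the mean. It acts on both randomized arms alike, so it adds noise but no bias between arms. Selection on the lumbar scan is itself only inferred, because the criterion names no skeletal site.
- A reader might infer that the plan wrongly omits site as a known source of variation. Nothing in the article shows that site predicts change in BMD; the two sites use the same type of machine, and no stratification by site is stated.

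The objection does not show that the unadjusted test is the better choice. In none of the scenarios worked through is ANCOVA less precise, apart from the one degree of freedom spent on the slope. An unseen plan may add adjusted analyses, but the article itself fixes the confirmatory test.

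**Conclusion.** The point holds as an inexpensive improvement. It does not show that the planned analysis is wrong. The direction is secure: adjusting for baseline lumbar BMD generally gives a more precise estimate of the same difference and takes out the part of a chance imbalance that subtraction leaves behind.

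The size is uncertain, from about 1–3% of variance to about 25%. It depends on the unstated rho, on equal variances at the two visits, and, for the power figures, on 0.097 being the SD of change. The upper part of the range should not be quoted without those conditions. The shift of 0.008 to 0.009 also needs its assumed SD of 0.1 and rho of 0.5. Any gain from a site term cannot be quantified from the document.

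**What to change.** Before unblinding, prespecify as the primary analysis an ANCOVA of week-12 L1–4 BMD (or of the change, which gives the same treatment estimate) on arm and baseline L1–4 BMD. Report the adjusted mean difference with its 95% CI. Keep Student's t-test or the Wilcoxon test of change as a supportive analysis. Use the same baseline adjustment for the continuous secondary endpoints. A site term is optional.

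No new data, visits or participants are needed. The cost is a dated, documented change to the analysis text. The confirmatory test is already stated in the published protocol and recruitment finished in April 2018, so the record must show that the change was made before the treatment codes were opened.

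### The confirmatory test of the primary endpoint is left open between Student's t-test and the Wilcoxon rank sum test, although the trial is sized on a mean difference

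*Protocol article*

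**What the plan says.** - **Endpoint** (Primary outcome measurement), defined in the article as follows: "The primary outcome will be the change in BMD at the lumbar spine (L1–4) between baseline (visit 1) and 12 weeks after randomization (visit 5").
- **Confirmatory test** (Statistical analysis): the change "between baseline and 12 weeks, will be evaluated using Student’s *t*-test or the Wilcoxon rank sum test". No rule for choosing follows in that sentence.
- **Nearest thing to a rule** (Statistical analysis, preceding paragraph): tests are chosen "depending on whether the data are normally distributed or skewed". This closes the sentence on the descriptive analysis. It names no normality test, significance level or threshold.
- **Sizing** (Sample size): "a mean difference of 0.047 ± 0.097 between the experimental group and control group was assumed", at 5% significance and 80% power, so that "a sample size of 66 patients per group would be necessary". Then: "Allowing for a dropout rate of 20%, a sample size of 168 participants (84 in each group) has been included".
- **Primary analysis set and missing data** (Statistical analysis): intention-to-treat, with missing values filled by LOCF.
- **BMD schedule** (Study plan): scans are described at screening and at visit 5 only. Under Data management, withdrawn women who agree still have the final-visit tests.

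**The concern.** One confirmatory hypothesis should have one test, fixed before the data are seen. Here there are two, and the choice between them has to be made from the outcome data by a rule that the article does not state.

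Three consequences follow.

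1. **Target.** The trial is sized on a difference in means. The rank sum test addresses whether values in one arm tend to exceed those in the other. Under a pure shift the two agree. This plan does not produce a pure shift: a woman with no visit 5 scan has only her baseline value to carry forward, so her change is exactly zero, and each arm becomes a mixture with a spike at zero.
2. **Power.** The rank test is somewhat less powerful than the t-test in such data, so the power actually achieved depends on which test is run.
3. **Flexibility.** If both tests are available and neither is named, the result can turn on the choice.

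**Working it through.** **Inputs.** Difference 0.047, SD 0.097, alpha 5%, power 80%, 66 per group, 20% dropout, 84 per group (all from Sample size); allocation "in a 1:1 allocation" (Design and setting). Assumptions made here: alpha is two-sided, 0.097 is the SD of the change, true changes are normal, and missingness is random and equal in both arms.

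**1. The plan's own figure.** n per group = 2 (1.96 + 0.842)² (SD/difference)² = 2 × 7.849 × (0.097/0.047)² = 2 × 7.849 × 4.259 = 66.9, so 67. The stated 66 gives 79.5% power, and 67/0.8 = 83.75, so 84. The planned size reproduces to within one patient, and it is a calculation for a comparison of means. If all 84 per group are scanned, power is 88.1%.

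**2. What LOCF zeros do to the comparison of means.** Let a share d of each arm have a change of exactly 0, with placebo mean 0:

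- difference = (1 − d) × 0.047
- placebo variance = (1 − d) × 0.097²
- BHH10 variance = (1 − d) × 0.097² + d(1 − d) × 0.047²

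At d = 0.20 the difference is 0.0376 and the SDs are 0.0868 and 0.0888. The standard error is √[(0.0868² + 0.0888²)/84] = 0.01354, the ratio is 0.0376/0.01354 = 2.776, and power is Φ(2.776 − 1.960) = 79.3%. At d = 0.10 the difference is 0.0423, the standard error 0.01428, the ratio 2.962 and power 84.2%.

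**3. Simulation of both tests.** 84 per arm, 4,000 trials per scenario, five placebo means from −0.047 to +0.02. Ranges are across placebo means.

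| Zeros per arm | t-test, formula | t-test, simulated | Wilcoxon, simulated |
|---|---|---|---|
| 0% | 88.1% | 88–89% | 86–87% |
| 10% | 84.2% | 82–84% | 79–82% |
| 20% | 79.3% | 77–79% | 73–75% |

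A separate rerun gave 88% and 86%, 84% and 81%, and 79% and 76% for the same three rows.

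**4. Splitting the loss.** From no zeros to 20% zeros the t-test alone falls from 88.1% to 79.3%, about 9 points. That part is LOCF. Moving from t-test to Wilcoxon at 20% zeros takes a further 3–5 points.

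**5. How often Wilcoxon would be chosen.** This depends on a rule that the article does not give:

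| Gate | 10% zeros | 20% zeros |
|---|---|---|
| Shapiro-Wilk 5%, either arm | about 30% | 85–86% |
| Shapiro-Wilk 1%, either arm | 10% | 59% |
| Lilliefors 5%, either arm | 53% | 99% |
| Skewness test 5%, either arm | 17% | 33% |

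The Shapiro-Wilk 5% gate at 20% zeros gives an overall power of about 75%.

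**6. Type I error and disagreement at 20% zeros.** With the choice fixed by the Shapiro-Wilk 5% gate, type I error was 4.9–5.4%. If both tests are run and the smaller p-value is reported, it is 6.3–6.5%. With a true difference of 0.047, the two tests disagree on significance in about 8–9% of trials.

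**The case against.** The strongest reply is that a journal article condenses the protocol, that the rule for choosing between a parametric and a rank test is commonly left to the SAP, and that a statistician blinded to allocation does the analysis. The null hypothesis is also worded as no difference in the change, which a rank test does address under a location shift. Part of this stands: the SAP may already name the test, and blinding limits steering. It does not remove the point. The article does not leave the primary test to another document; it states it as an either/or. Blinding does not prevent both p-values from being computed on masked groups.

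A reader might go further and infer that LOCF zeros will usually force the Wilcoxon test, and that the plan therefore delivers about 75% power instead of 80%. The documents do not support that, for three reasons.

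- The 20% is a planning allowance for dropout, not a forecast of missing scans, and withdrawn women may still be scanned at the final visit. At 10% zeros Wilcoxon power is about 79–82%, essentially the planned level.
- No normality test is named. The article's own word is skewed, and a skewness check selects Wilcoxon in only about a third of trials even at 20% zeros.
- Most of the shortfall is LOCF dilution, which also brings the t-test to about 79%. Changing the test does not recover it.

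Nor is an inflated type I error built into the plan. The 6.3–6.5% applies only if the more favourable p-value is picked, and nothing in the article provides for that.

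**Conclusion.** The point holds in a limited form. The confirmatory test of the only primary endpoint is not fixed, and one of the two candidates does not match the mean difference on which the trial was sized once LOCF zeros enter the data. The choice of test is worth about 2 points of power with complete scans and 3–5 points at 20% zeros, and in that worst case it could change the trial's conclusion in about 8–9% of trials. The 75% figure for Wilcoxon belongs to that worst case only and should be quoted with its condition. These sizes rest on normal true changes, equal random missingness in the two arms, a two-sided 5% level and 0.097 read as the SD of the change. This is a weakness in prespecification that should be closed before unblinding. It does not make the planned sample size wrong.

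**What to change.** Before unblinding, replace the either/or with one named test, in the SAP and in the protocol if it is amended. For example:

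> *The primary analysis compares mean change in L1–4 BMD from visit 1 to visit 5 between groups by ANCOVA with baseline L1–4 BMD as covariate, two-sided at 5%, and is used regardless of the observed distribution. The Wilcoxon rank sum test is a sensitivity analysis.*

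If an unadjusted analysis is preferred, name a Welch t-test instead. With about 67 or more observed per arm, a comparison of means is robust to moderate skewness, so no normality gate is needed.

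The cost is one sentence. Baseline lumbar BMD is already collected, and no patients, visits or data are added. The downside is slight: if changes prove heavy-tailed, the rank test could be somewhat more efficient, and the sensitivity analysis would show this. The change does not repair the dilution caused by LOCF, which is a separate matter.
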